#### **Temporary modifications to data collection during COVID-19 pandemic**

Due to the COVID-19 pandemic and social distancing orders, the following modifications will be made until research operations allow adequate in-person contact.

1. Data collection surveys as described above will be conducted by telephone with the possibility of using Doximity (HIPAA secured videohealth) in some occasions.
2. Subjects will be compensated for data collection visits with a gift card instead of cash. Gift cards will be purchased online from major online retailers and mailed directly to subjects.
3. Subjects will be offered the option to complete the Hemoglobin A1c test and Cholesterol panel at home using FDA-approved home test kits from Home Access Health Corporation. Each test requires a finger stick using a lancet (provided) to produce 5 drops of blood for the sample. The total time required to complete the tests is 20-30 minutes. The following steps will be taken to inform subjects about the kits and obtain results remotely.
  - a. Data collectors will call subjects to provide details about the kits and determine if they are willing and able to complete the lab tests at home.
  - b. If so, coordinator will prepare one of each kit to be mailed to the subject. Coordinator will sanitize work surfaces thoroughly and wear gloves and a mask while packaging any kits.
  - c. Each kit has an identification number which will be linked to the subject's study ID. Home Access also requires a date of birth (DOB) to identify each sample. To protect the subject's PHI, we will create a master list with shifted DOBs for subjects using the REDCap date shifting feature. With this feature, REDCap randomly shifts dates up to 364 days upon downloading the data. The shifted DOB and the study ID will be used to label the kits.
  - d. A list of assigned kits with shifted DOBs and study IDs will be sent to Home Access via a secure FTP (SFTP) server. No PHI will be sent to Home Access.
  - e. The subjects will complete the tests with guidance from the data collector (over the phone or Doximity) and mail them to the lab using the prepaid envelope provided by Home Access.
  - f. Samples will be processed by Home Access and results will be sent daily to coordinator via SFTP server.
  - g. A \$20 gift card for completing the home test kits will be sent to subject once a result is confirmed.

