*Phlebotomy:* Subjects may have pain or bruising at the site where blood is drawn for phlebotomy. Less common risks include fainting, the formation of a small blood clot or swelling of the vein and surrounding tissue, bleeding from the site, and infection. The Clinical Interface Core (CIC) employs health professionals for all phlebotomy services. *Home test kits:* Subjects may experience very brief discomfort after the finger stick and from squeezing drops of blood into the sample well. This will be comparable to the pain they experience when they undergo glucose testing. Alcohol pads, gauze and bandaids are provided with each kit to keep the site clean. Tips for minimizing discomfort and increase blood flow are included in the kit and instructional video online.

While unlikely, there is a slight risk that a participant may indicate thoughts of suicide or self-harm by scoring a 2 or 3 on item 9 of the PHQ-9 questionnaire. If this occurs, the data collector will contact [name] on her cell phone immediately upon completion of the interview or during a break in the interview (if appropriate). [name] is a trained clinical psychologist and as such will come to the CIC, meet with the patient and evaluate if further action is needed to ensure the participant’s safety. If [name] is unable to be reached, [name] will be paged or reached by cell phone. [name] or [name] will assess the participant including suicidal ideation, intent, and plan. Then, [name] or [name] will intervene appropriately, which may include providing resources for mental health support, facilitating referral to psychiatry, or immediately escorting the participant to the UI Health emergency room if urgent evaluation/intervention is needed to ensure personal safety, security, and stability.

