### **8.0 Data Collection and Management Procedures**

Physiological and Survey Measures: The UIC Center for Clinical Translational Science (CCTS) Clinical Interface Core (CIC) will provide data collection services for all physiologic measures. Trained study RAs will conduct all surveys by interview in the CIC, in English or Spanish. These staff will receive training and practice on specific techniques for establishing professional rapport, answering potential questions, and maintaining cooperation of respondents. Laminated cards with Likert-type scale responses are provided as a visual reference to patients. RAs possess laptop computers and remotely access REDCap for data entry. The survey requires an average duration of 60 minutes. Subjects will receive compensation as previously described (Section 6.2) for travel and time at each collection point. Public transit cards will be provided when needed.

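### The response to a PHQ-9 item 9 score of 2 or 3 was not adapted to telephone and video surveys: it still rests on a meeting at the CIC and a physical escort, and nothing establishes where the participant is or keeps them on the line.

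*Protocol*

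**What the plan says.** **The item 9 procedure.** Section 7.0 of the protocol (Risks and Protections) is the only text on a score of 2 or 3 on PHQ-9 item 9. The data collector rings the first-line clinician's cell phone "immediately upon completion of the interview or during a break in the interview (if appropriate"). That clinician "is a trained clinical psychologist and as such will come to the CIC, meet with the patient and evaluate if further action is needed". A backup is paged or called if the first cannot be reached. Whichever clinician responds assesses ideation, intent and plan and "will intervene appropriately, which may include providing resources for mental health support, facilitating referral to psychiatry". The one further action on that list, and the only one given for urgent need, is "immediately escorting the participant to the UI Health emergency room if urgent evaluation/intervention is needed".

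**Where surveys take place.** Section 8.0 gives the ordinary setting: "Trained study RAs will conduct all surveys by interview in the CIC, in English or Spanish". The PHQ-9 is one of the time-varying measures in that section, collected at 0, 6, 12, 18 and 24 months.

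**The COVID-19 change.** Section 6.1 (Temporary modifications to data collection) says that "the following modifications will be made until research operations allow adequate in-person contact". The first of these is: "Data collection surveys as described above will be conducted by telephone with the possibility of using Doximity (HIPAA secured videohealth) in some occasions".

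**The concern.** The item 9 procedure was written for a participant sitting in the CIC. That setting supplied two safeguards without their being written down: staff knew where the participant was, and the participant was on site while the clinician was being reached. Once the survey is done by telephone, both are lost and the protocol puts nothing in their place. If a remote participant is at urgent risk, help could be delayed because there is no confirmed place to send it, or because the participant must first be reached again. The possible harm is serious and may be irreversible, even if the event is rare.

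**Working it through.** No arithmetic applies. The check sets each step of the item 9 procedure (section 7.0) against the remote survey mode (section 6.1), then looks through the rest of the protocol for anything that fills the gap.

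**Can item 9 be answered remotely?** Yes. The modification covers the data collection surveys as a whole, the PHQ-9 is part of them, and no text exempts it.

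**Does each step survive the change of mode?**

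| Step in section 7.0 | Participant in the CIC | Participant on the telephone |
|---|---|---|
| Alert by cell phone, at the end of the interview or in a break | Participant still on site | Works, but the call may be over before the alert is made |
| First-line clinician comes to the CIC for a meeting | Works | Cannot take place |
| Assessment of ideation, intent and plan | Works | Possible; no mode is fixed |
| Resources or psychiatric referral | Works | Possible; no mode is fixed |
| Escort to the emergency room for urgent need | Works | Unavailable; no alternative is named |
| Knowing where the participant is | Implicit | Not provided for |

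**Does anything else in the protocol supply the missing pieces?**

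- Section 6.1 (Retention) and the Transition and Retention text provide for periodic checks of contact data. These are retention measures and do not give the participant's location during a call.
- The Pharmacy Management Protocol, part A, mentions emergency contacts on file, for patients who miss pharmacist visits.
- Section 6.4 lists telemedicine practice points, but for pharmacist videoconferences and not for research surveys.
- Section 11.0 has staff report participants' problems to the co-principal investigators, which is general reporting.
- The Pharmacy Management Protocol, part D, directs a patient to the Emergency Department as a last resort when a pharmacist needs physician input.
- The other COVID-19 texts deal with laboratory tests, payment and contact by intervention staff. None mentions item 9.

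None of these establishes current location or keeps the participant on the line.

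**Deliberate or overlooked?** The paragraph of section 7.0 just before the item 9 text already covers finger-stick discomfort from the home test kits, which came in with the COVID-19 modification. The section was therefore updated for remote collection and the item 9 steps were not. This looks like an oversight.

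**The case against.** The strongest reply is that most of the procedure already works by phone. The trigger, the alert, the backup and the required assessment all carry over. Only the first-line clinician is tied to the CIC. The list of actions is open-ended, so a clinician may already assess by telephone and send emergency help. All of that is correct, and it limits the point: the protocol does not forbid an adequate remote response.

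A second reply is that a location check and an instruction to stay on the line are interviewer-script details that may sit in forms not shown. That possibility cannot be excluded. But the protocol itself fixes this procedure in detail, and two of the steps it fixes cannot be carried out remotely, so the text needs correcting whatever a script says.

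Third, the alert may be made during a break, and nothing says the participant is released before the clinician is called. True, but the break is optional, and no sentence requires the line to stay open. In the CIC the participant is still on site when the interview ends; on the telephone the call may simply be over.

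Fourth, addresses are verified periodically and people living outside Chicago for 3 or more months a year are excluded. An address on file is a usable starting point, but it does not show where the participant is at the time of the call.

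Finally, the event is described as unlikely and the remote period is temporary. That bears on how often the gap would matter, not on whether the written steps can be followed when it does.

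**Conclusion.** The concern holds. During the remote period the protocol's stated first-line step and its only named urgent step cannot be carried out, and the two things a remote response depends on, a known location and an open line, are not provided for. Clinician discretion softens this but cannot supply a location nobody asked for or bring back a participant who has hung up.

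The size cannot be put in numbers. The documents give neither the number of remote interviews nor a rate of item 9 scores of 2 or 3, and section 7.0 calls the event unlikely and the risk slight. Exposure is limited to the temporary remote period. No trial estimate is affected. The conclusion assumes that the PHQ-9 stays in the remote survey, as the text implies, and that no operating procedure outside the protocol already covers these steps. It should be fixed, as a matter of participant safety.

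**What to change.** Add the following, for remote interviews only, to the COVID-19 modification in section 6.1 or to the item 9 text in section 7.0:

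1. At the start of the call, the data collector confirms the participant's current location and a call-back number.
2. On an item 9 score of 2 or 3, the data collector keeps the participant on the line while the clinician or the backup is reached.
3. The clinician assesses by telephone or Doximity in place of the CIC meeting.
4. If the clinician judges the risk urgent, emergency services are sent to the confirmed location in place of the escort.

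The score threshold and the clinician's discretion stay as they are.

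The cost is a short amendment and one extra question per remote call. The clinician and backup are already designated. Data collectors already work remotely: for the home kits, "The subjects will complete the tests with guidance from the data collector (over the phone or Doximity)". Holding the participant while ringing the clinician may need a second line or a conference call, which is a minor practical matter.

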### Benefits

This study may provide additional, generalizable knowledge regarding the impact of the mHealth diabetes adherence support intervention, including HCs and clinical pharmacists in helping minority groups with uncontrolled diabetes. The expectations are that all subjects may potentially benefit from the support provided. In the United States, underserved African-American and Latino populations are disproportionately affected by type 2 diabetes and face greater barriers utilizing conventional health care. Many do not achieve their goals of normal blood sugar and blood pressure and remain at high risk for complications when compared with Whites. The discovery of newer approaches to improve their blood sugar and blood pressure control is needed. This study includes HCs, pharmacists and mobile health technology that

combined may make these support services more accessible to this vulnerable population. In addition, this study will examine the cost and cost-effectiveness of mHealth diabetes adherence support. The risks taken on behalf of subjects are small compared with the importance of the knowledge gained in this study.

#### **Additional Benefits of mDAS Sleep Sub-Study Supplement:**

Patients will have no direct benefit from participation in the sleep sub-study. However, it will contribute to scientific knowledge related to the challenges underserved African-American and Latino populations face in diabetes care, poor sleep duration and quality, which may contribute to worse diabetes-related health outcomes. Data exploring sleep quality within minority populations is very limited. Existing data suggest that African-Americans and Latinos are more likely to have poor sleep quality due to either psychosocial stress or non-standard sleep hours contributing to inconsistent sleep patterns and an increased risk of diabetes. Further sleep research involving minority populations with diabetes is needed for discovery of better treatment options.

At the end of the study, each participant will receive a thank you letter with a synopsis of their sleep results. Each participant will receive their average number of hours of sleep per night, the target number of hours of sleep they should aim for per night, and some general sleep hygiene tips.

### **8.0 Data Collection and Management Procedures**

Physiological and Survey Measures: The UIC Center for Clinical Translational Science (CCTS) Clinical Interface Core (CIC) will provide data collection services for all physiologic measures. Trained study RAs will conduct all surveys by interview in the CIC, in English or Spanish. These staff will receive training and practice on specific techniques for establishing professional rapport, answering potential questions, and maintaining cooperation of respondents. Laminated cards with Likert-type scale responses are provided as a visual reference to patients. RAs possess laptop computers and remotely access REDCap for data entry. The survey requires an average duration of 60 minutes. Subjects will receive compensation as previously described (Section 6.2) for travel and time at each collection point. Public transit cards will be provided when needed.

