### 3.0 Objectives/Aims

We propose a randomized, controlled trial to evaluate the effectiveness of an mHealth Diabetes Adherence Support (*mDAS*) intervention delivered by clinical pharmacists and health coaches. This proposal is in response to NIH PA-14-334: Advancing Interventions to Improve Medication Adherence. We will randomize 220 patients through the University of Illinois Hospital & Health Sciences System (UI Health) to either: (1) mHealth diabetes adherence support (*mDAS*) through clinical pharmacists and HCs; or (2) usual care. After one year, patients completing the mHealth adherence intervention will be monitored for an additional year while the usual care group receives *mDAS*.

The specific aims include:

- Aim 1:** To evaluate the *effectiveness* of *mDAS* delivered by clinical pharmacists and HCs to African-American and Latino adults with uncontrolled type 2 diabetes. We will compare *mDAS* and usual care through the following outcome measures: hemoglobin A1c, blood pressure, LDL-cholesterol levels, and medication adherence.
- Aim 2:** To evaluate the *maintenance* of improved clinical outcomes and medication adherence one year after intervention completion.
- Aim 3:** To evaluate the cost and cost-effectiveness of *mDAS* compared to usual care.
- Aim 4:** To evaluate *reach, adoption, and implementation* of *mDAS* (RE-AIM framework)

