### **6.1 Overview of Participant Procedures**

#### Recruitment and Randomization

1. Potential participants will be identified by one of four recruitment methods previously described.
2. RAs will screen patients for eligibility and discuss the study protocol in detail. If the patient is deemed eligible to participate he/she will complete written informed consent and HIPAA authorization.

3. Enrolled participants will schedule an appointment at the UIC Clinical Interface Core (CIC) to complete baseline data collection, which includes a blood draw.
4. Participants randomized to *mDAS* will receive the intervention component in Year 1, while participants randomized to *Usual Care* will receive it in Year 2. RAs will inform participants of assignment.

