#### Evaluation of Pharmacist Activity and Medication Changes

1. Chart review by a research assistant will define the number of PCP and pharmacist encounters as well as the number of pharmacist- or physician-initiated medication changes.

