### **Transition and Retention**

Despite having "access" to healthcare, participants will be economically vulnerable individuals with uncontrolled diabetes. Ethically, we acknowledge that the "usual care" currently received often does not meet patients' needs or standards of care. Therefore, participants assigned to usual care will receive initial support to engage existing resources available through UI Health, such that healthcare providers will consider this an acceptable alternative upon randomization (clinical equipoise).

Upon randomization, participants will receive referrals to a diabetes educator and clinical pharmacist for medication reconciliation, adherence support, and education. Staff can schedule the visit at data collection. This is important as our prior work with medication reconciliation identified discrepancies in almost 60% of patients. A one-page list of clinic resources with names and direct telephone numbers (e.g., social worker) will be provided so they can more easily navigate the system. Finally, low-literacy, paper-based diabetes education information will be provided. At the end of year 1, these patients will cross-over and receive *mDAS*. Prior to this transition, HCs will work with the patients and their social support network to prepare them for the transition. Participants randomized to usual care will receive *mDAS* for one year.

*Retention strategies.* Participants will be reimbursed \$30 for each data collection. Participants assigned to the intervention in year one will receive an additional \$50 at 6 months and 12 months if they complete at least one videoconference before each data collection. Participants assigned to the intervention in year two will receive an additional \$50 at 18 months and 24 months if they complete at least one videoconference before each data collection. Participants who complete all five data collection visits and videoconferences with the pharmacist as described above will receive up to \$250 for completing the study.

*Additional Retention Strategies for mDAS Sleep Sub-study Supplement* Participants will be reimbursed an additional \$40 for participating in the sleep sub-study and turning in the wrist actigraph.

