3. *PCP and Pharmacist Activity:* The pharmacist will reconcile medications as part of the intervention, and the reconciled list from the medical chart will be used as data

to evaluate medication changes and overall complexity of therapy. Intensification of therapy will be defined as the number of increases in the dosage of antihypertensive, hypoglycemic agent, or insulin or the addition of a new agent since the baseline visit. Chart review will define the number of PCP visits and pharmacist videoconferences as well as the number of pharmacist- or physician-initiated medication changes.

4. *Patient Summary Evaluation*: Feedback will be collected from participants regarding their experience with the health coach, pharmacist, and videoconference technology. Individual responses will not be shared directly with the participant's health coach or pharmacist. Evaluation will be collected at 12 months for participants who receive the intervention in Year 1 or 24 months for those who receive it in Year 2.

Physiologic Outcomes and Quality of Life: Physiologic outcomes will be collected at five time points (0, 6-, 12-, 18-, and 24-months). CIC research staff will perform phlebotomy, blood pressure, weight and height recordings while being blinded to subject group assignment.

1. *Hemoglobin A1c and fasting lipid profile* (total cholesterol, HDL, LDL, and triglycerides) will be obtained via phlebotomy. The A1c laboratory test has National Glycohemoglobin Standardization Program certification.
2. A calibrated digital scale will measure *weight*.
3. At baseline, a height stadiometer will measure body *height*, with subjects removing their shoes (for BMI assessment).
4. *Blood pressure* will be assessed on subjects sitting down for at least five minutes, following standard procedure. Extreme blood pressures are reported to [name] per CIC protocol.
5. *Health Related Quality of Life* will be measured using the EQ5-D (general) and DDS4 (diabetes specific).

Medication Adherence and Behavioral Outcomes: Medication adherence will be assessed using self-report and objective measures.

1. A self-report *medication adherence* survey will be included for all diabetes medications (developed by Lu et al, AIDS Behav 2008; Gonzalez JS et al, Diabetes Care, 2013). This instrument includes three items.

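### Research assistants both disclose allocation and conduct all survey interviews, and nothing masks those who take the follow-up surveys: a gap that is cheap to narrow

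*Protocol*

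**What the plan says.** The relevant statements are spread over several sections of the protocol.

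- **Disclosure of the arm.** Section 6.1, Recruitment and Randomization: "RAs will inform participants of assignment".
- **Surveys.** Section 8.0, opening paragraph: "Trained study RAs will conduct all surveys by interview in the CIC, in English or Spanish".
- **Blinding.** Section 8.0, Physiologic Outcomes and Quality of Life: "CIC research staff will perform phlebotomy, blood pressure, weight and height recordings while being blinded to subject group assignment".
- **Adherence as an outcome.** Aim 1 in Section 3.0 compares the arms on "hemoglobin A1c, blood pressure, LDL-cholesterol levels, and medication adherence".
- **How adherence is measured.** Section 8.0: "Medication adherence will be assessed using self-report and objective measures". The self-report part is a three-item survey. The objective part is the proportion of days covered (PDC) from pharmacy fills, which the protocol rates as the more valuable of the two.
- **Chart review.** Section 6.1, Evaluation of Pharmacist Activity and Medication Changes: "Chart review by a research assistant will define the number of PCP and pharmacist encounters".

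Two further procedures are tied to the data collection visits and differ by arm. Under Transition and Retention, a $50 videoconference bonus can be earned at months 6 and 12 in the arm treated first, and at months 18 and 24 in the other. Under Section 8.0, Process Measures, item 4, participants evaluate the coach, pharmacist and videoconferencing at month 12 or month 24, depending on arm.

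**The concern.** The measures most open to an interviewer's influence are the answers given aloud in an interview. Those are the measures for which the protocol states no masking. An RA who knows that a patient has had months of coaching on adherence may probe, prompt or record differently from one who does not know. In this setting the shift would plausibly favour mDAS on adherence, self-care, self-efficacy and social support, although the documents do not establish its direction.

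The credibility of the self-reported results is at stake. Self-reported adherence is half of the measurement of an Aim 1 outcome. Self-efficacy and social support are candidate mediators in Section 12.0, tested at a relaxed alpha of 0.10, and both are collected by interview. Who discloses the arm and who assesses outcomes is a matter for the protocol, and here the protocol assigns both to one role.

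**Working it through.** The protocol states no figure on this point, so the check sets the provisions side by side.

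1. **Who knows the arm?** RAs as a role do, because Section 6.1 has them tell participants. The sentence sets no limit on which RAs.

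2. **Who interviews?** RAs as a role, for all surveys (Section 8.0). During the COVID-19 modifications in Section 6.1 the same surveys move to the telephone, and no masking is added.

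3. **Does any provision separate or mask them?** None does. The one assessor-blinding sentence is confined to clinical core staff and four physical procedures. The coded subject number in Sections 7.0 and 13.0 is a confidentiality measure, and it cannot mask someone who is talking to the participant.

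4. **Would the arm be visible at follow-up even if another RA had disclosed it?** Possibly, by three routes:
   - the videoconference bonus, although the protocol does not say who administers it;
   - the coach and pharmacist evaluation, which reveals the arm at month 12, before the month 18 and 24 surveys;
   - the chart review of pharmacist encounters, if the reviewing RA also interviews.

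5. **Which visits are exposed?** Section 6.0 places allocation after consent and baseline data collection. The exposed surveys are those at 6, 12, 18 and 24 months.

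6. **Which outcomes are exposed?**

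| Measure | Source | Exposed to interviewer expectation? |
|---|---|---|
| Self-reported adherence, SDSCA | RA interview | Yes |
| PHQ-9, EQ5-D, DDS4 | RA interview | Yes |
| Self-efficacy, social support | RA interview | Yes |
| PDC | Pharmacy records | No |
| A1c, LDL | Laboratory sample | No |
| Blood pressure | Blinded core staff | No |

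7. **How large is the bias?** That would need the between-arm shift that interviewers induce on each scale. The documents give no such figure and nothing from which to derive one.

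**The case against.** The strongest reply is that the trial's main inferences are protected. Sample size rests on A1c. The primary analysis in Section 12.0 concerns the physiological outcomes jointly, and the maintenance hypothesis names A1c, blood pressure and LDL. Adherence has a record-based companion that the protocol already prefers. QALYs are to come from a Markov model, so EQ5-D matters less than it may seem. Mediation is examined only if the intervention works. Interviewers are trained and use response cards. All of this stands, and it keeps the point modest. Training and cards standardise the questions but do not mask the person asking them.

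A second reply is that participants know their arm, so masking interviewers leaves respondent bias untouched. That is correct. Masking would also leak: the survey asks about support from the healthcare team, and some participants will volunteer their arm. Interviewer bias can be reduced, not removed.

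Three stronger readings are tempting but unsupported:

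- **That the same individual discloses the arm and then interviews that participant.** The protocol names a role, not individuals. Section 13.0 has a bilingual RA consent all Spanish-speaking participants, which makes overlap likelier for them but does not establish it.
- **That referral scheduling reveals the arm at follow-up.** The sentence "Staff can schedule the visit at data collection" stands in a paragraph about referrals made upon randomization, and it refers to staff in general.
- **That the bias amounts to a known rise in false positives.** With 88 completers per arm (220 × 0.8 / 2), the standard error of a standardised difference is √(2/88) = 0.151. An assumed shift of 0.10 or 0.20 SD would then raise a two-sided 5% error rate to about 10% or 26%. Those shifts are assumptions with no basis in the documents, so the rates are not estimates for this trial.

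**Conclusion.** The point holds as a cheap improvement. As written, the protocol gives disclosure of the arm and all survey interviews to one role, and limits assessor blinding to physical measures. It therefore leaves the interviewer-administered scales at 6, 12, 18 and 24 months open to interviewer expectation.

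The conclusion that interviewers may know the arm rests on three things: the shared role, the absence of any masking or separation, and the visit procedures that can reveal the arm. It does not rest on a statement that interviewers are unblinded. No size is claimed. Baseline surveys, A1c, blood pressure, LDL and PDC are unaffected, so a reader should not infer that the powered comparison is compromised.

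**What to change.** 1. **Section 6.1, Recruitment and Randomization.** Have the project coordinator, a written notice, or (in the mDAS arm) the health coach at first contact disclose the assignment instead of the RAs. A written notice in Spanish would serve Spanish-speaking usual-care participants.
2. **Transition and Retention.** Have the coordinator handle the videoconference bonus.
3. **Section 8.0 and the COVID-19 data collection modifications.** State that RAs taking follow-up surveys, in person or by telephone, are not told the arm and ask participants not to disclose it.
4. **Section 8.0, Process Measures, item 4.** Take the coach, pharmacist and videoconference evaluation after all outcome scales, preferably by someone who will not interview that participant again.
5. **Section 6.1, chart review.** Assign it to staff who do not interview the same participants, or do it after their last survey.
6. **Section 8.0, adherence.** Name PDC as the main adherence measure and self-report as supporting.

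The cost is some added coordinator time and a reordered survey, with no new staff or visits. Masking will be incomplete, because some participants will reveal their arm.
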